#### 2. TITLE OF PROTOCOL:

SERUM 25(OH)D LEVELS, SUPPLEMENTAL VITAMIN D, AND PARATHYROID HORMONE LEVELS IN PREMATURE INFANTS

## SECTION II

**Instructions:** In order to review your proposal, the IRB must have the following information pursuant to its charge by federal regulations for the protection of human subjects. Each subpart must be titled using numbered **boldface subheadings** as described below and addressed independently in the listed sequence without reliance on information covered under other subparts. Attachment of applicable sections of the grant application or detailed protocol is not acceptable as a substitute for completion of each subpart.

*The IRB Application must provide sufficient information to facilitate an effective review by all members of the IRB including non-specialists. There is an educational guide to this application available on the IRB website titled “**Educational Guide – Biomedical Research (PedsIRB)**”. Questions that have an educational note that explain the information requirements will be referred to the Guide with the statement “See Educational Guide – Biomedical Research (PedsIRB)”. Applications that do not allow for an effective review may be returned to the investigator, without IRB review, for revision and resubmission.*

### **PROTOCOL ABSTRACT**

**Provide a brief (less than 400 words) abstract of the research protocol. This summary should include: 1) the title of the protocol, 2) a *brief* description of the purpose of the study, 3) eligibility criteria, 4) interventions and evaluations and 4) follow-up.**

#### **Serum 25(OH)D levels, Supplemental Vitamin D, and Parathyroid Hormone Levels in Newborn Hospitalized Infants**

Low maternal serum 25(OH)D levels have documented negative repercussions on the skeletal health of the newborn. Parathyroid hormone (PTH) levels are often used as a marker of vitamin D sufficiency, however 25(OH)D levels to achieve suppression of PTH levels in premature infants is unknown. In addition, recent evidence has shown that vitamin D insufficiency (defined as 25(OH)D levels of <30 ng/mL) is an important risk factor in for neonates and children acquiring infections such as RTI and pneumonia.

The specific aims of this study are to determine levels of vitamin D supplementation to achieve goal serum 25(OH)D levels of 30 ng/mL, and to define serum 25(OH)D levels required to achieve suppression of parathyroid hormone in preterm newborn infants hospitalized in the Nebraska Medical Center Newborn Intensive Care Nursery (NICU). In this randomized, controlled trial, infants 23 weeks gestational age or greater will be randomized to two different levels of vitamin D supplementation: 400 IU vitamin D3/day, or 800 IU vitamin D3/day. As an exploratory aim, vitamin D binding protein levels (VDBP) and term corrected age DEXA scan to evaluate bone mineralization will also be quantified in these infants.

This research is innovative because while vitamin D research is occurring in many arenas, few investigators have ethical access to a population of hospitalized infants, including infants born prematurely. Bone health is a special concern in this population. A high percentage of bone mineralization takes place in the last trimester of pregnancy, and premature infants should be rapidly mineralizing bone. While a high prevalence of vitamin D deficiency is being documented in this population, less is known about vitamin D's relationship with PTH. We seek to define intakes of vitamin D that will result in goal

25(OH)D levels, and of serum concentrations of 25(OH)D that will suppress PTH in a population of hospitalized, premature infants.

## **PURPOSE OF THE STUDY AND THE BACKGROUND (1-2)**

### **1. PURPOSE OF THE STUDY**

**What are the specific scientific objectives (aims) of the research?**

- Primary Specific Aims:
  - To investigate a dose of vitamin D supplementation necessary to achieve goal 25(OH)D levels of 30 ng/mL in a population of premature infants during their NICU hospitalization.
  - To determine the serum 25(OH)D level required to achieve suppression of parathyroid hormone in a population of premature, hospitalized infants.
- Secondary Specific Aims:
  - As a secondary, exploratory aim, vitamin D binding protein and its relationship with 25(OH)D levels will be measured and quantified in a population of premature, hospitalized infants. A term corrected age DEXA scan to evaluate bone mineral content will also be performed.

### **2. BACKGROUND AND RATIONALE**

**Describe the background of the study. Include a critical evaluation of existing knowledge, and specifically identify the information gaps that the project is intended to fill. [See Educational Guide – Biomedical Research \(PedsIRB\)](#)**

Infants are completely dependent on the maternal supply of vitamin D, and an infant will be born with 25(OH)D levels that are approximately 80% of the mother's circulating 25(OH)D levels.(2) With recent evidence that a large percentage of the population of women of child-bearing age, and especially African-American women, are vitamin D deficient or insufficient, newborns are at high risk for vitamin D deficiency. (3-5)

Low serum 25(OH)D levels have documented negative repercussions on the skeletal health of the newborn. Infants of vitamin D deficient mothers show splaying of the distal metaphysis of the femur and the presence of craniotables in utero and at birth, both of which are consistent with rickets and lower bone mass relative to body weight at birth (6-8). These deficits persist into the first decade of life, with an increase in bone mineral mass at 8 years of age in vitamin D supplemented infants (9), and a decrease in bone mineral content at 9 years of age in children whose mothers were vitamin D deficient (10). Parathyroid hormone (PTH) is often used as a marker of bone turnover, and an inverse relationship between PTH and 25(OH)D levels has been documented in many studies (11-14). Studies in adolescents show that serum 25(OH)D levels of 36 ng/mL are necessary to suppress PTH levels (14). In addition, recent evidence has shown that vitamin D insufficiency (defined as 25(OH)D levels of <30 ng/mL) is an important risk factor in neonates and children acquiring infections such as respiratory tract infection (RTI) and pneumonia (15,16). Cord blood 25(OH)D levels have been shown to impact innate immune responses (17).

Very little is known about the primary carrier protein of vitamin D, vitamin D binding protein (VDBP) in premature infants. A study conducted in the 1980s show some evidence that VDBP may increase with increasing gestational age (18). These investigators will quantify VDSP in this population, and hypothesize VDSP levels will increase with increased vitamin D supplementation.

### CHARACTERISTICS OF THE SUBJECT POPULATION (3-10)

#### 3. ACCRUAL

- A. What is the number of subjects that must complete the study and be evaluable in order to achieve the scientific objectives of the research?** [See Educational Guide – Biomedical Research \(PedsIRB\)](#)

40 NICU infants who are between 23 and 32 weeks gestational age must complete the study.

- B. What is the statistical or other justification for the number of subjects needed to complete the study?** [See Educational Guide – Biomedical Research \(PedsIRB\)](#)

Based on our previous study, NICU infants who received 400 IU/day of Vitamin D are expected to have a mean discharge serum 25(OH)D of 23.1 ng/ml (standard deviation=7.0). Conservatively, the 800 IU dose group is expected to have a mean discharge serum 25(OH)D of 30 ng/ml (SD=7.0) (SD estimated from our previous study data). Assuming a 0.05 level of significance, and a total drop-out rate of 10 percent; 40 NICU infants randomized to the two dose groups will provide 81 percent power to detect a difference between doses.

- C. What is the maximum number of subjects that will be consented at all sites under the oversight of the PedsIRB and what is the justification for this number?** [See Educational Guide – Biomedical Research \(PedsIRB\)](#)

A maximum of 40 infants who are between 23 and 32 weeks gestational age will be consented for the study.

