## METHODS AND PROCEDURES (11-15)

### 11. METHODS AND PROCEDURES APPLIED TO HUMAN SUBJECTS

- A. Does this protocol require tests to be performed for the purpose of determining subject eligibility which would not be *routinely* conducted as part of standard clinical care of the prospective subject?

☒ No

☐ Yes. Describe the tests to determine subject eligibility. [See Educational Guide – Biomedical Research \(PedsIRB\)](#)

- B. Indicate the study design by checking the appropriate boxes.

[See Educational Guide – Biomedical Research \(PedsIRB\)](#)

☐ Phase I

☐ Phase I/II

☐ Phase II

☐ Phase II/III

☐ Phase III

☐ Phase IV

☐ Other:

☐ Case-Control

☐ Cohort

☐ Cross-sectional

☐ Randomized, parallel group

☐ Randomized, cross-over

☐ Placebo-Controlled

☐ Single Blind

☒ Double Blind

☐ Triple Blind

- C. Describe sequentially all procedures, interventions and evaluations to be applied to subjects, including follow-up. [See Educational Guide – Biomedical Research \(PedsIRB\)](#)

Step 1: Recruitment and Informed Consent

Parents of infants admitted to the NICU who meet eligibility criteria will be approached by study personnel, information about the study will be given, and informed consent will be obtained.

Step 2: Collection of Baseline Data

A sample of cord blood drawn that is drawn at birth for other routine clinical use will be frozen and stored at -70 degrees for study analysis of 25(OH)D levels. Demographic information will be obtained, including gestational age, birth weight, length, circumference, race, ethnicity, and season of birth. This is routine NICU admission information that is not performed exclusively for research purposes.

Step 3: Randomization

Study pharmacist will be notified and eligible infants will be randomized to the 400 IU/day of 800 IU/day supplementation group. Vitamin D supplementation will begin when the infant reaches full enteral feedings. Both the investigators and the subjects will be blinded as to the treatment group.

Step 4: NICU Data Collection

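### Section 3 gives 40 as the number completing, randomised and consented; with its own 10% drop-out only 36 complete, and the 81% power rests on those 36

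*Protocol*

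**What the plan says.** Section 3 of the protocol (Accrual) answers three different questions with the same number.

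- **3.A**, on how many subjects must finish and be evaluable for the objectives to be met: "40 NICU infants who are between 23 and 32 weeks gestational age must complete the study".
- **3.B**, the sample size justification, assumes "a total drop-out rate of 10 percent" and states that "40 NICU infants randomized to the two dose groups will provide 81 percent power to detect a difference between doses". The 400 IU infants "are expected to have a mean discharge serum 25(OH)D of 23.1 ng/ml (standard deviation=7.0") and "the 800 IU dose group is expected to have a mean discharge serum 25(OH)D of 30 ng/ml (SD=7.0").
- **3.C**, on the maximum number consented: "A maximum of 40 infants who are between 23 and 32 weeks gestational age will be consented for the study".

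Two other sections bear on the drop-out figure. Section 26.D says the investigators anticipate no withdrawals, since infants are inpatients and the risk is low. Section 18.E lists several grounds for withdrawal, including a request by the parent or neonatologist, certain diagnoses and treatments, and laboratory abnormalities.

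**The concern.** The numbers completing, randomised and consented can be equal only if no infant is lost at any stage. Section 3.B assumes that 10% are lost. Under that assumption the requirement in 3.A is not expected to be met within the cap in 3.C, and the number behind the power statement differs from the number that 3.A calls necessary.

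The IRB is therefore told that the objectives need 40 completers when the plan's own justification needs 36. A trial that ends with 36 or 37 completers would look short of its target although it had met its power assumption.

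A second mismatch lies between 3.B and 3.C. The power needs 40 infants randomised, but the cap counts consents. Any infant consented and then not randomised uses one of the 40 places, and nothing in the section provides for replacement.

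**Working it through.** **Inputs.** Means 23.1 and 30 ng/mL, SD 7.0 in both groups, significance level 0.05, total drop-out 10%, 40 randomised (section 3.B). Two-sided tests (section 11.E). The allocation ratio is not stated; 1:1 is assumed.

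**Step 1: expected completers.** 40 × (1 − 0.10) = 36, or 18 per arm.

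**Step 2: reproduce the stated power.** The difference is 30 − 23.1 = 6.9. For a two-sample t-test with n per arm, the noncentrality is 6.9 / (7.0 × √(2/n)) on 2n − 2 degrees of freedom.

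| Evaluable | Per arm | Noncentrality | Power, t-test | Power, normal approximation |
|---|---|---|---|---|
| 36 | 18 | 6.9 / (7.0 × √(2/18)) = 2.96 | 81.9% | 84.1% |
| 40 | 20 | 6.9 / (7.0 × √(2/20)) = 3.12 | 85.9% | 87.6% |

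The stated 81% agrees with 36 evaluable infants by the t-test to within one percentage point. With 40 evaluable, both methods give a figure about 5 points or more above 81%. So 3.B has already taken off the 10%.

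**Step 3: what 40 completers would require.** 40 / 0.90 = 44.4, so 45 randomised. That exceeds the consent cap of 40 by 5.

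**Step 4: chance of 40 completers under the cap.** If each infant had an independent 10% risk of dropping out, the chance that all 40 complete is 0.90^40 = 0.015, about 1.5%.

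**Step 5: the drop-out statements side by side.** Section 3.B plans for 10% loss, section 26.D anticipates none, and section 18.E sets out how losses may arise. Section 3.A fits only the expectation in 26.D, and the power in 3.B fits only the 10%.

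**The case against.** The strongest reply is that no calculation in the plan is wrong. Section 3.B is consistent within itself: 40 randomised, 36 evaluable, about 81% power. The cap in 3.C fits it if every consented infant is randomised. On this view 3.A merely carries the randomised number in the place of the completer number. That stands, and it limits the point to a wrong stated requirement and a cap with no margin.

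It can also be said that 40 of 40 is possible, since section 26.D anticipates no withdrawals. That is fair against any claim that 40 completers is impossible. It does not settle the matter, because 3.A would then rest on zero loss and 3.B on 10% loss, within the same section.

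A reader might infer more: that the trial is underpowered because parents are approached around admission (section 27.A) whereas "Vitamin D supplementation will begin when the infant reaches full enteral feedings", so that some consented infants never start. The protocol does not support this as a finding. It gives no rate for such losses, and the 10% in 3.B is described as a total. Not starting the supplement is also not the same as being lost to analysis: section 11.E specifies intention to treat, and section 11.C times the blood draws from birth and at 36 weeks corrected age, not from the first dose. Only infants consented but never randomised are lost outright. As an illustration, if an assumed 10% of the 40 consented were never randomised, 40 × 0.9 × 0.9 = 32.4. With 32 evaluable (16 per arm) the t-test power is 77.0%. With no such loss it stays at 81.9%.

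**Conclusion.** The point holds as an inconsistency in the stated sample size. Under the plan's own 10% drop-out, 40 consented and randomised infants leave 36 completers, so 3.A overstates the required number by 4 and its figure cannot be expected within the cap in 3.C. The 81% rests on 36 evaluable infants (81.9%), not 40 (85.9%). This assumes 1:1 allocation and a two-sided t-test.

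It would be wrong to conclude that the power statement is mistaken or that the primary comparison is underpowered: if 36 infants complete, the stated power stands. The mismatch between a cap on consents and a power based on randomised infants is real, but its effect on power cannot be sized from the protocol. The time of randomisation relative to full feeds is not stated, and correcting these numbers does not require changing it.

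**What to change.** 1. In 3.A, state that 36 evaluable infants (18 per arm) are needed. Keep 40 randomised, 10% drop-out and 81% power in 3.B.
2. In 3.C, give 40 as the number randomised and add an explicit maximum number of consents that allows for infants consented but never randomised. The form asks for a consent number, so giving only the randomised number would leave its question unanswered. The investigators should state the loss they assume between consent and randomisation.
3. Reconcile the 10% in 3.B with the expectation of no withdrawals in section 26.D and the withdrawal criteria in section 18.E, so that one loss assumption runs through the document.

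If 40 completers are really wanted, the alternative is to keep 3.A, raise the number randomised to at least 45 with a consent ceiling no lower than that, and restate the power as about 86%.

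The preferred change leaves the randomised size, the power and the analysis as they are. It costs wording in three sections and IRB agreement to a consent ceiling above 40, with perhaps a few more families approached.

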#### 4. GENDER OF THE SUBJECTS

- A. Are there any enrollment restrictions based on gender?**

- ☒ No  
☐ Yes. Provide justification. [See Educational Guide – Biomedical Research \(PedsIRB\)](#)

**B. Are individuals of childbearing potential excluded from participation in this study?**

- ☐ No  
☒ Yes. Provide justification. [See Educational Guide – Biomedical Research \(PedsIRB\)](#)  
The study is on infants

**C. Are pregnant individuals excluded from participation?**

- ☐ No  
☒ Yes. Provide justification. [See Educational Guide – Biomedical Research \(PedsIRB\)](#)  
The study is on infants

**D. Are breast feeding individuals excluded from participation?**

- ☐ No  
☒ Yes. Provide justification. [See Educational Guide – Biomedical Research \(PedsIRB\)](#)  
The study is on infants

**5. AGE RANGE OF SUBJECTS**

**A. What is the justification for inclusion of children in this research?**

The rationale for the age range included is to add to the current body of knowledge regarding the vitamin D intake required in a population of premature infants to achieve goal 25(OH)D levels and suppression of PTH.

**B. What is the age range for the child subjects, and what is the justification for selecting this age range?** [See Educational Guide – Biomedical Research \(PedsIRB\)](#)

The age range of the subjects will be between 23 and 32 weeks gestational age. This age range will expand upon a previous study completed by these investigators that showed a mean 25(OH)D level of 17 ng/mL in infants greater than 32 weeks gestational age, and recent results by other investigators that show a high prevalence of deficiency in this population. Based on those results, and data that supports a high prevalence of vitamin D deficiency in pregnant women, we seek to define intakes that will promote optimal 25(OH)D levels in a wide population of premature infants.

**C. Will this study enroll wards of the state?**

- ☒ No  
☐ Yes. Complete the [Addendum H - for Research Involving Children Who Are Wards](#).

**D. Will adults (19 years of age or older) be included in this research?**

- ☒ No  
☐ Yes. Provide the age range and justification for their inclusion for the stated age range and complete and attach [Addendum Y](#).

**6. RACE AND ETHNICITY**

**Are there any subject enrollment restrictions based upon race or ethnic origin?**

- ☒ No  
☐ Yes. Explain the nature of the restrictions and provide justification. [See Educational Guide – Biomedical Research \(PedsIRB\)](#)

## 7. VULNERABLE SUBJECTS

A. Will any of the following vulnerable populations be included in this research? [See Educational Guide – Biomedical Research \(PedsIRB\)](#)

| No                                  | Yes                      | Vulnerable Population                                                            | Complete:   |
|-------------------------------------|--------------------------|----------------------------------------------------------------------------------|-------------|
|  |  | Pregnant individuals, fetuses or neonates (non-viable or of uncertain viability) | Addendum B1 |
|  |  | Prisoners                                                                        | Addendum C  |

B. Will any other vulnerable population be specifically recruited for enrollment in this research

- ☒ No  
☐ Yes.

1. Who are the vulnerable subjects that will be specifically recruited for enrollment? [See Educational Guide – Biomedical Research \(PedsIRB\)](#)

2. Describe the additional protections which will be in place. [See Educational Guide – Biomedical Research \(PedsIRB\)](#)

## 8. INCLUSION CRITERIA

What are the specific inclusion criteria? [See Educational Guide – Biomedical Research \(PedsIRB\)](#)

Infants who are receiving inpatient care in the Newborn Intensive Care Nursery will be considered for enrollment. Prospective subjects who are between 23 and 32 weeks gestational age will be identified on admission to the Nebraska Medical Center Newborn Intensive Care Nursery.

## 9. EXCLUSION CRITERIA

What are the specific exclusion criteria? [See Educational Guide – Biomedical Research \(PedsIRB\)](#)

Exclusion criteria will be infants receiving, congenital abnormalities, GI, liver, or kidney disease, inborn errors of metabolism, parathyroid disease, and disorders of calcium metabolism, and infants receiving seizure medication or steroids. Infants whose parents are less than 19 years of age will also be excluded from the study, to avoid obtaining parenteral consent from a parent who is not legal adult age in the state of Nebraska. Infants who are made wards of the State of Nebraska will also be excluded from the study, per Nebraska State law 390 NAC 11-002.04K which states wards of the state may not participate in medical research unless a specific exception is granted by the state, following an evaluation of the protocol by staff in the Medical and Legal Divisions of the Nebraska Health and Human Services System.

## 10. CONTRACEPTION REQUIREMENTS

Are there any specific contraception requirements?

- ☒ No  
☐ Yes. Describe the requirements and provide justification. [See Educational Guide – Biomedical Research \(PedsIRB\)](#)

## METHODS AND PROCEDURES (11-15)

### 11. METHODS AND PROCEDURES APPLIED TO HUMAN SUBJECTS

- A. Does this protocol require tests to be performed for the purpose of determining subject eligibility which would not be *routinely* conducted as part of standard clinical care of the prospective subject?

☒ No

☐ Yes. Describe the tests to determine subject eligibility. [See Educational Guide – Biomedical Research \(PedsIRB\)](#)

- B. Indicate the study design by checking the appropriate boxes.

[See Educational Guide – Biomedical Research \(PedsIRB\)](#)

☐ Phase I

☐ Phase I/II

☐ Phase II

☐ Phase II/III

☐ Phase III

☐ Phase IV

☐ Other:

☐ Case-Control

☐ Cohort

☐ Cross-sectional

☐ Randomized, parallel group

☐ Randomized, cross-over

☐ Placebo-Controlled

☐ Single Blind

☒ Double Blind

☐ Triple Blind

- C. Describe sequentially all procedures, interventions and evaluations to be applied to subjects, including follow-up. [See Educational Guide – Biomedical Research \(PedsIRB\)](#)

Step 1: Recruitment and Informed Consent

Parents of infants admitted to the NICU who meet eligibility criteria will be approached by study personnel, information about the study will be given, and informed consent will be obtained.

Step 2: Collection of Baseline Data

A sample of cord blood drawn that is drawn at birth for other routine clinical use will be frozen and stored at -70 degrees for study analysis of 25(OH)D levels. Demographic information will be obtained, including gestational age, birth weight, length, circumference, race, ethnicity, and season of birth. This is routine NICU admission information that is not performed exclusively for research purposes.

Step 3: Randomization

Study pharmacist will be notified and eligible infants will be randomized to the 400 IU/day of 800 IU/day supplementation group. Vitamin D supplementation will begin when the infant reaches full enteral feedings. Both the investigators and the subjects will be blinded as to the treatment group.

Step 4: NICU Data Collection

Blood samples will be drawn every 4 weeks, beginning 4 weeks after birth. The maximum amount of blood taken at each blood draw will be 2 mL. The final blood draw will occur at 36 weeks CGA. Analysis of each blood sample will include 25(OH)D levels, PHT levels, and VDBP. A serum calcium will be obtained with each blood draw for safety monitoring purposes, if not already available from routine NICU lab monitoring. Lab draws in the NICU are done by the nursing staff and are done using heelstick or venipuncture, at the discretion of the nursing staff. Nurses may make more than one

attempt to draw blood, but if the lab draw cannot be successfully completed, the attempt is terminated at the discretion of the bedside nurse. Ongoing clinical data collection from the patients' medical record will include daily vitamin D intake, growth parameters, and infections/antibiotic use.

Step 5: Urine collection and DEXA Scan: When the infant reaches 36 weeks gestational age, a 24-hour urine sample will be obtained for measurement of calcium excretion. At 40-44 weeks gestational age, a DEXA scan will be performed.

| Test                                  | Frequency of Collection                                                                     | Amount of Blood                                                                                                                                                                                                                                                                    |
|---------------------------------------|---------------------------------------------------------------------------------------------|------------------------------------------------------------------------------------------------------------------------------------------------------------------------------------------------------------------------------------------------------------------------------------|
| 25(OH)D(ng/mL)                        | Collected on cord blood, every 4 weeks, and at 36 weeks CGA                                 | Requires < 0.5 mL                                                                                                                                                                                                                                                                  |
| Serum Calcium (For safety monitoring) | Collected with each 25(OH)D draw                                                            | Will be collected for study purposes only when not drawn as part of routine NICU labs (requires 0.5 mL)                                                                                                                                                                            |
| PTH                            | Collected with each 25(OH)D draw                                                            | 1 mL                                                                                                                                                                                                                                                                               |
| VDBP                           | Collected with each 25(OH)D draw                                                            | 0.1 mL (included in the 0.5 for 25(OH)D)                                                                                                                                                                                                                                           |
| TOTAL                          | Max blood draws on any 1 infant, not including cord blood: Every 4 weeks from 24-36weeks: 3 | 2 mL maximum every 4 weeks A volume of 4 mL in 8 weeks will allow an infant with a weight of 1300 grams to remain within the guidelines of 3 mL/kg of blood for study purposes in an 8 week period. Protocol adjustments will be made to minimize blood volumes in smaller infants |

**D. Identify any procedures, interventions, and evaluations that are experimental or performed exclusively for research purposes. *See Educational Guide – Biomedical Research (PedsIRB)***

Procedures performed exclusively for research purposes include:

1. Acquisition and storage of cord blood for analysis.
2. Blood samples taken every 4 weeks for analysis of 25(OH)D, iPTH, serum calcium, and VDBP.
3. 24 hour urine collection for calcium excretion
4. DEXA scan after discharge at term corrected age

24-hour urine collection for 24 hour calcium excretion will be collected using an infant urine collection bag that is placed in the infants' diapers. The bags are attached to the skin as per the manufacturer's instructions and are changed with every diaper change to minimize any risk of skin breakdown.

A serum calcium levels will be run on the blood sample for study purposes only if the infant does not have a serum calcium level available at the time point (within 72 hours) of the study draw. NICU hospitalized infants have routine clinical monitoring of laboratory values and this routinely includes serum calcium levels. If a serum calcium level is available, it will be used as the value for study purposes, and will decrease the amount of blood required for study purposes.

Guidelines used for blood draw limits for this study was 3 mL/kg over an 8 week period. This volume would allow an infant with a birth weight of 1.3 kg to complete our protocol as written. If the birth weight of the infant is less than 1.3 grams, the volume allowed for the study over the next 8 weeks will be calculated and protocol adjustments will be made. Examples of protocol modifications will be: use of clinically available serum calcium, if not available, ionized calcium could be used for safety monitoring purposes with less than 0.3 mL of blood. The investigators

could also eliminate the VDBP assay in this infant (as this is an exploratory aim) to reduce the amount of blood needed. 25(OH)D on the volume of blood remaining after a CBC is run, this option could be investigated to reduce blood draw volume.

**E. Describe briefly the statistical methods used to analyze the data.** [See Educational Guide – Biomedical Research \(PedsIRB\)](#)

The primary endpoint for statistical analysis is serum 25(OH)D level at discharge. Analysis will be done using intent-to-treat strategy, where infants will be included in the group to which they were assigned regardless of compliance. The statistical analyses will be done with SAS software. P-values less than 0.05 will be considered statistically significant. Baseline characteristics (e.g. gender, season of birth) will be compared between the dose groups, stratified by race and gestational age, to ensure comparability of the groups using Mann-Whitney tests for continuous variables and Fisher's exact tests for categorical variables. Analysis of covariance (ANCOVA) will be conducted to test for differences in discharge serum 25(OH)D level between the dose groups while adjusting for known confounders (race, gestational age, gender and season of birth). If the overall F-tests are significant then pairwise comparisons will be made and p-values for these comparisons will be adjusted for multiple comparisons using Tukey's method. Correlation methods will be used to look at associations between 25(OH)D levels and iPTH levels at discharge. Descriptive plots will be used to evaluate changes in serum 25(OH)D levels. DEXA scan results evaluating total body minus head bone mineral density (BMD) will be compared between the two groups. Descriptive plots will be used to evaluate changes in serum 25(OH)D levels. All tests will be 2-sided and p-values <0.05 will be considered statistically significant.

